### Data analysis

2.7

Repeated measures models will be performed comparing the results of the three groups according to the study variables, clinical, cognitive, metacognitive, and social functioning, social stigma, motor coordination, physical health status, as well as biomarker variables. We will include as covariates those variables that show significant mean differences between groups in the baseline assessment. Additionally, we will control by sex, age, antipsychotic dose (chlorpromazine levels) and symptom severity, since these are variables that have been associated with our main outcomes.

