
On one hand, we expect that WA intervention will improve physical health variables. On the other hand, we expect that MCT will improve variables related to symptoms and metacognition. Therefore, our main hypothesis is that the combined intervention will enhance the benefits of WA and MCT separately. The project will aim to evaluate the effects of each intervention, comparing the changes in the explored variables between the 3 intervention groups. Specifically, it is expected that the combined intervention will greatly facilitate an improvement in symptoms, cognition, metacognition, and psychosocial functioning. In addition, the transcript levels of the SP1 and SP4 biomarkers may change after the interventions, and it is anticipated that these changes will be even greater when the two interventions are combined.

The objectives of this project are:

To evaluate the efficacy of a combined intervention (WA and MCT) in people with schizophrenia or other psychotic disorders compared to each of the independent interventions on:Psychotic symptoms, cognition, metacognition, psychosocial functioning, and social stigmaMotor coordinationState of physical health: weight, height, BMI, abdominal circumference, blood pressure, heart rate, analysis that includes information on glucose, total cholesterol, HDL, and LDLStudy changes in the transcription levels of the SP1 and SP4 biomarkers depending on the intervention received (WA, MCT or combined intervention).Associate changes in SP1 and SP4 levels to improvements in symptoms, cognition, metacognition, social functioning, social stigma, motor coordination, and physical health status.

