### Study design

2.1

This is a unicentric randomized controlled trial with 3 parallel intervention groups. Participating services will recruit patients, and they will be randomized to each condition. Following baseline assessment, a random number table is used to assign each patient to one of the three conditions.

Conditions are (1) MCT, (2) WA, and (3) Combined Intervention (MCT and WA). The interventions include 8 weekly sessions, lasting approximately 2 months. We will perform post-treatment assessments right after the treatment ends. Upon completion of the last assessment, patients will be offered the opportunity to participate in any of the activities, regardless of the group assigned during the 2-month intervention. Details on the flowchart of the study can be seen in Supplementary Figure S1.

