### Data collection

2.4

A trained psychologist will perform baseline and post-treatment assessments of sociodemographic, clinical, functioning, metacognitive and social cognitive variables. Each assessment will consist of 2–3 interviews. Nursing staff will take anatomical measures and conduct hemograms from the cubital vein for the separation of peripheral blood mononuclear cells. The blood will be processed by the molecular psychiatry laboratory on the same day as the hemogram and will be stored at −80°C until molecular analysis.

This study is in accordance with the World Medical Association’s Declaration of Helsinki and was approved by the Sant Joan de Déu Ethics Committee (Reference: PIC-155-21). The study will involve human participants and we will obtain informed consent prior to the start of the assessments. The staff performing the assessments, hemograms and molecular analyses will be blind to the study condition assigned to the participants. All variables will be measured at baseline and after the 2-month intervention, except the WAIS-III Vocabulary subscale, which will only be administered at baseline. After the 2-month intervention, we will collect qualitative data on patient satisfaction with the intervention, based on a questionnaire created *ad hoc*.

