### Sample size calculation

2.6

Based on previous results obtained in a MCT efficacy clinical trial (Ochoa et al., 2017) and accepting an alpha risk of 0.05 and a beta risk of less than 0.2 in a bilateral contrast, we would need 48 subjects to detect a difference equal to or greater than 1.7 units in the BCIS metacognitive variable, assuming a SD of 3.63. A loss to follow-up of 25% has been estimated.

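### With one baseline and one post-treatment value per outcome, section 2.7 should adjust every outcome for its own baseline; comparing change is valid but less precise

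*Protocol article*

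**What the plan says.** All references are to the protocol article.

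- **Design (2.1 Study design):** "This is a unicentric randomized controlled trial with 3 parallel intervention groups".
- **Measurement times (2.4 Data collection):** "All variables will be measured at baseline and after the 2-month intervention". Apart from one vocabulary subscale taken only at baseline, each measure therefore has two values.
- **Aim (1 Introduction):** the effects are to be evaluated by "comparing the changes in the explored variables between the 3 intervention groups".
- **Model (2.7 Data analysis):** "Repeated measures models will be performed comparing the results of the three groups".
- **Covariates (2.7):** "We will include as covariates those variables that show significant mean differences between groups in the baseline assessment". In addition, "we will control by sex, age, antipsychotic dose (chlorpromazine levels) and symptom severity".
- **Sizing (2.6 Sample size calculation):** 48 subjects, for a difference of 1.7 units in the BCIS with an SD of 3.63, "accepting an alpha risk of 0.05 and a beta risk of less than 0.2 in a bilateral contrast". "A loss to follow-up of 25% has been estimated".

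Nothing in section 2.7 says that each outcome is routinely adjusted for its own baseline, or that the arms share one baseline mean in the model.

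**The concern.** Randomised arms have the same expected baseline, so any observed baseline difference D between two arms is chance. A change-score comparison subtracts the whole of D. The best prediction of what D contributes to the post value is only rho × D, where rho is the baseline-to-post correlation. The change-score estimate is therefore off by −(1−rho)D in that realisation. Over repeated randomisations this averages to zero, so it is noise and not bias, but ANCOVA removes it from data already in hand.

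Under the covariate rule in 2.7, an outcome gets this adjustment only when a baseline significance test happens to be positive, or when the outcome is itself the symptom-severity covariate. The BCIS, on which the trial is sized, is not assured of it. At stake is precision in a trial with roughly 12 completers per arm.

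**Working it through.** **Inputs from the article:** three arms; two measurement times; N = 48; difference 1.7; SD 3.63; two-sided alpha 0.05; power at least 0.80; 25% loss.

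**Assumptions:** equal allocation (16 per arm); 48 already includes the loss, leaving 16 × 0.75 = 12 completers per arm; the same SD s at both times; rho varied, because the article gives none. Section 2.6 does not say whether 3.63 is the SD of change or the SD at one time point, so both readings are shown.

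**1. The plan's own figure.** A single-group (paired) calculation gives n = (3.63 × (1.960 + 0.842) / 1.7)² = 35.8, rounded up to 36, and 36 / 0.75 = 48. The stated total is reproduced. A between-arm contrast needs n = 2 × 3.63² × (1.960 + 0.842)² / 1.7², which is 72 per arm. That gap is a separate problem; it matters here because it shows how little precision there is to spare.

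**2. Group-by-time equals change score.** On one simulated data set (3 × 12, two times, complete), the repeated-measures group-by-time test and a one-way ANOVA of change scores both gave F = 2.696, p = 0.0823. Adding the outcome's baseline to the change-score model gave F = 2.900, p = 0.0696, identical to ANCOVA of the post value.

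**3. Variance ratio.** Per participant:

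- change score: 2(1−rho)s²
- ANCOVA: (1−rho²)s²
- ratio: (1−rho²) / (2(1−rho)) = (1+rho)/2

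The difference between the two variances is 2(1−rho) − (1−rho²) = (1−rho)² in units of s², which is the chance-imbalance term described above.

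**4. Cost of estimating the slope at 12 per arm.** The within-arm degrees of freedom are 36 − 3 = 33. Estimating the slope inflates the ANCOVA variance by 1 + 1/(33−2) = 32/31 = 1.032. Simulation (20,000 replicates) agrees:

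| rho | (1+rho)/2 | × 32/31 | simulated |
|---|---|---|---|
| 0.3 | 0.65 | 0.67 | 0.67 |
| 0.5 | 0.75 | 0.77 | 0.77 |
| 0.7 | 0.85 | 0.88 | 0.88 |
| 0.8 | 0.90 | 0.93 | 0.93 |
| 0.9 | 0.95 | 0.98 | 0.98 |
| 0.95 | 0.975 | 1.01 | 1.00 |

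Break-even is at (1+rho)/2 × 32/31 = 1, that is rho = 62/32 − 1 = 0.94.

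**5. On the protocol's target.** Pairwise contrast of 1.7 by normal approximation, without the 32/31 factor. The n per arm is for 80% power; power is at 12 completers per arm, Φ(1.7 / (SD × √(2/12)) − 1.960). Each cell reads change score → ANCOVA.

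| rho | n/arm, 3.63 = SD of change | power | n/arm, 3.63 = SD at one time | power |
|---|---|---|---|---|
| 0.3 | 72 → 47 | 20.8% → 29.6% | 101 → 66 | 16.1% → 22.4% |
| 0.5 | 72 → 54 | 20.8% → 26.3% | 72 → 54 | 20.8% → 26.3% |
| 0.7 | 72 → 61 | 20.8% → 23.7% | 43 → 37 | 31.6% → 36.2% |
| 0.9 | 72 → 68 | 20.8% → 21.7% | 15 → 14 | 72.7% → 74.9% |

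**The case against.** **The model is not spelled out.** Section 2.7 never names a group-by-time term, and a mixed model with a common baseline mean is itself a repeated measures model. A condensed article may leave the model's form to a fuller document. This stands as a limit: if that model is what is meant, the fix only makes it explicit. But the article does fix two measurement times, a comparison of changes, and a covariate rule that makes own-baseline adjustment conditional. That rule is stated, not left open.

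**Adjustment is partly there.** An outcome whose baseline differs significantly does enter as a covariate, and symptom severity is always controlled, which may serve the symptom outcomes. True, but neither route assures adjustment for the BCIS or for most other outcomes.

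**The gain may be small.** Weight, BMI and cholesterol over 2 months in stable patients could plausibly have high rho, where little is gained. This also stands, and it is why the range above runs to 0.95.

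A reader might infer more than the documents support:

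- *That a group main effect, diluted by the baseline value, will be tested.* No section plans this, and the Introduction speaks of comparing changes.
- *That the control for sex, age, dose and severity cancels out.* That holds only if covariates enter as main effects alone in a long-format model. The article does not say so, and the classical multivariate form lets covariates act at each time point.
- *That the proposed model would rescue the expected 25% loss.* It would not. With a common baseline mean, that mean cancels from the 2-month arm contrast, and the slope comes from completers. In a simulated check with 4 of 16 post values missing per arm, the contrast was 0.6686 with everyone, with completers only, and by completer ANCOVA.

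**Conclusion.** The point holds as one of efficiency. The comparison of change is a valid test, unbiased under randomisation; it is not wrong, only less precise than the same data allow. With 12 completers per arm, routine adjustment for the outcome's own baseline cuts the variance of an arm contrast by about 33%, 23%, 12% and 2% at rho 0.3, 0.5, 0.7 and 0.9, and by nothing from about 0.94 upward.

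These sizes rest on assumed rho, equal allocation, equal SDs at both times, and 48 including the loss. They also rest on reading 2.7 as an unconstrained model whose between-arm test is the comparison of change.

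It would be wrong to infer that the change repairs the sample size. At rho 0.5, power for 1.7 units moves from 20.8% to 26.3%, well short of 80% either way.

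**What to change.** State in section 2.7 that each 2-month outcome is compared between the three arms by ANCOVA, adjusting for that outcome's own baseline value and the fixed covariates (sex, age, antipsychotic dose, symptom severity). An equivalent mixed model with a common baseline mean across arms would serve equally well. Say that this applies to every outcome with a baseline value, whatever the baseline significance tests show. Where the outcome is itself the symptom-severity measure, its baseline is entered once.

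The cost is a sentence and a line of model code: no extra patients, visits or measurements. The sample-size calculation and the handling of missing post values need their own attention; this change addresses neither.

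### Beyond four pre-named covariates, further ones are added by testing the randomised groups for baseline differences, so the model depends on chance imbalances; fix the full list in advance

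*Protocol article*

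**What the plan says.** Section 2.7 (Data analysis) describes the model in general terms: "Repeated measures models will be performed comparing the results of the three groups according to the study variables". It then gives two covariate rules.

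- The first selects on a test: "We will include as covariates those variables that show significant mean differences between groups in the baseline assessment".
- The second selects on prognosis: "Additionally, we will control by sex, age, antipsychotic dose (chlorpromazine levels) and symptom severity". The reason given is "since these are variables that have been associated with our main outcomes".

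The second rule applies whatever the tests show. The final model therefore holds four fixed covariates plus whatever the baseline tests flag. Section 2.1 (Study design) says that allocation follows the baseline assessment and uses a random number table.

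**The concern.** Under randomisation the null hypothesis of a baseline test is true by design. A small p-value marks a chance imbalance and nothing more. Adjustment is worth its degrees of freedom when a variable predicts the outcome, and the first rule does not look at that. The second rule does, so the section uses a sound criterion and an unsound one side by side.

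Three things follow:

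- The covariate set cannot be written down until the baseline data have been seen.
- Variables unrelated to outcome enter at the nominal 5% rate each. They enter precisely because they are associated with group, which is the kind of covariate that most widens the standard error of a group contrast.
- The test does not reliably catch imbalances that matter, because only large differences reach significance in arms this small.

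**Working it through.** **Number of completers.** Inputs from section 2.6 (Sample size calculation): two-sided alpha 0.05, beta 0.2, difference 1.7, SD 3.63, loss 25%.

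- (3.63 × (1.960 + 0.842) / 1.7)² = 35.8, so 36.
- 36 / (1 − 0.25) = 48, the stated total.

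The plan's own figures therefore imply 36 completers. The allocation ratio is not stated; 1:1:1 is assumed here, giving 16 randomised and 12 completing per arm. (This is a one-group formula. Whether it suits a three-group comparison is a separate matter.)

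**Chance of a false flag.** For k independent candidates tested at 0.05, P(at least one) = 1 − 0.95^k, and the expected number flagged is 0.05k.

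| k | P(at least one) | expected number |
|---|---|---|
| 5 | 0.23 | 0.25 |
| 10 | 0.40 | 0.5 |
| 20 | 0.64 | 1.0 |
| 40 | 0.87 | 2.0 |

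The article does not give k. Section 2.3 (Measures) names ten somatometric, cardiovascular and metabolic measures, plus SP1 and SP4 at protein and mRNA level. That makes 14 before any clinical or cognitive scale, so 10 to 20 is a reasonable range. Correlation among candidates lowers the probability of at least one flag but not the expected number.

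**What the test can detect.** In a two-arm t-test, the smallest significant difference is t(0.975; 2n − 2) × √(2/n). This is 0.72 SD at n = 16 and 0.85 SD at n = 12.

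**Cost in precision.** Simulation of 15,000 trials per setting: 12 completers per arm, change-score form of the two-time model, and four forced covariates each weakly related to outcome. One of the k candidates is the outcome's own baseline and the rest are irrelevant. Candidates enter if a three-group F-test gives p < 0.05. The entries are the empirical standard error of an arm contrast, in SD units.

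| pre-post correlation | k | four only | four + flagged | ratio |
|---|---|---|---|---|
| 0.5 | 10 | 0.402 | 0.405 | 1.01 |
| 0.7 | 10 | 0.291 | 0.296 | 1.02 |
| 0.5 | 20 | 0.400 | 0.421 | 1.05 |
| 0.7 | 20 | 0.290 | 0.308 | 1.06 |

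The mean model-based standard error gives ratios of 1.03 (0.407/0.397 and 0.296/0.287) for k = 10 and 1.06 (0.420/0.396 and 0.305/0.287) for k = 20. When every candidate is irrelevant the cost is somewhat higher, because no useful variable can be picked up. Allowing for that, the range is about 1–3% for 10 candidates and 5–8% for 20. A check run with only irrelevant candidates fell inside the second range and slightly above the first, so these are approximate figures.

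**Power and type I error.** At the planned effect, 1.7 / 3.63 = 0.47 SD, dropping the tested covariates moves power from 0.19 to 0.20 at correlation 0.5, and from 0.32–0.33 to 0.34–0.35 at 0.7. Type I error with the tested covariates was 0.046–0.051.

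**Fixing the outcome's own baseline.** With the four covariates plus the baseline outcome always in the model, the standard error is 0.343 at correlation 0.5 and 0.264–0.265 at 0.7. Against these, the testing rule costs 0.296/0.264 = 1.12 up to 0.421/0.343 = 1.23. Power becomes 0.26–0.27 and 0.40–0.41. This is an upper reading: a repeated-measures model already uses the baseline outcome as a response, and the gain depends on how the model is set up.

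**The case against.** The best defence is that the core of the model is already right. The four covariates most likely to matter are forced in for the reason a statistician would give, and the tests can only add to them. A reader might infer that all covariates are chosen by testing, or that these four could be dropped. The text rules that out.

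The defence also holds on validity. The tests use baseline data only, so the rule as written is not steered by outcome results, and the simulations show no inflation of type I error.

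A reader might also infer a large loss of precision by comparing the rule with a model that always adjusts for a strong predictor outside the four. The documents name no such predictor, and a list of the four would not adjust for it either. In a simulation with an unlisted predictor correlated 0.5 with outcome, the variance of the pairwise difference was 0.129 if always adjusted, 0.157 under the testing rule and 0.163 if never adjusted. In that scenario deleting the rule is slightly worse (0.163 / 0.157 = 1.04). This is a real, small cost of the change.

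Finally, a reader might infer that symptom severity and antipsychotic dose would be adjusted for at their post-treatment values, since "All variables will be measured at baseline and after the 2-month intervention, except the WAIS-III Vocabulary subscale". The article does not say so. The sentence follows directly on one about the baseline assessment, and covariate timing is a detail that a condensed article may leave to the full plan. That reading is not supported.

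What the defence does not answer is why a significance test on randomised groups should decide which further variables enter.

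**Conclusion.** The point stands in a limited form. Beyond four properly chosen covariates, section 2.7 admits others on a criterion that is chance by construction. The model is not fixed in advance and some of its degrees of freedom go to variables that do not predict outcome. The supported cost is about 1–3% in standard error with 10 candidates and 5–8% with 20, or one to three points of power at the planned effect, plus whatever precision is forgone by not fixing the outcome's own baseline.

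No bias and no type I inflation has been shown.

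The sizes rest on assumptions that the article does not settle: 1:1:1 allocation, 10 to 20 independent candidates, pre-post correlation of 0.5 to 0.7, and covariates that act on the change between visits. If covariates enter without a time interaction in a balanced model, the group-by-time estimate may hardly move. The loss of pre-specification remains in every case.

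**What to change.** Delete the sentence on baseline differences and state one list for every model: sex, age, baseline chlorpromazine-equivalent dose and baseline symptom severity, with severity omitted where it is the outcome's own baseline. Say how the outcome's own baseline is handled: either as a covariate in an ANCOVA of the post-treatment value, or as a response in a repeated-measures model whose baseline means are constrained equal across arms. Report baseline characteristics by arm descriptively, without tests.

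The cost is one or two sentences in section 2.7, with no extra data and no burden on participants. Two consequences should be acknowledged. Naming ANCOVA or a constrained model settles the form of the model, so it is more than a wording change. And a chance imbalance in an unlisted variable would no longer be adjusted for in the main analysis; it can be shown in a sensitivity analysis labelled as such.

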## Expected results and discussion

3

To the best of our knowledge, this is the first study to investigate the effectiveness of a combination of MCT and WA in a sample of people with psychosis. Additionally, this is the first study that evaluates changes in the transcriptional biomarkers SP1 and SP4 after the implementation of these interventions.

If the hypotheses of this study are confirmed, they have dual applicability. On the one hand, the evidence shows how MCT improves psychotic symptoms, especially positive symptoms, cognitive insight, cognition, and cognitive biases (Penney et al., 2022). On the other hand, physical exercise can improve psychotic symptoms, neurocognition, social functioning, social stigma, motor coordination and several physical health parameters (Firth et al., 2018). Specifically, WA would be a promising option for the comprehensive treatment of psychosis. We hypothesize that the combination of both interventions can optimize the benefits that each has separately. Also, the combination of MCT and WA could influence changes in biomarkers related to psychosis. This would reflect the importance of considering gene reprogramming for the treatment to be effective. Therefore, this article would support the need to combine psychological interventions and physical exercise to improve mental health.

Most researchers and clinicians agree that the treatment of patients with psychosis should be personalized and adapted to their specific needs (Package of Interventions for Rehabilitation, 2023). However, this is seldom done in clinical practice. One of the reasons is the economic cost of tailored treatments. Another important reason is the lack of scientific knowledge on the grounds that should guide the personalization of interventions. This is a current challenge in research in mental health. MCT is a perfect candidate to study its viability as a personalized treatment for several reasons. Firstly, it has proven its short-and long-term efficacy (Moritz et al., 2014; Ochoa et al., 2017; Penney et al., 2022) and it is currently included as a treatment of choice for people with psychosis in therapeutic guidelines and targets the psychological foundations of psychosis (Package of Interventions for Rehabilitation, 2023). Secondly, it has been studied in different subpopulations of psychosis showing positive results in different diagnoses and stages of the illness. Additionally, different profiles of patients could benefit from MCT considering their baseline assessment (Ferrer-Quintero et al., 2021, 2022). Thirdly, it is standardized through a manual guide, that allows comparison between different hospitals and facilitates delivery by any mental health professional with adequate training. Finally, the intervention is conducted in a group setting, thus being more cost-effective than individual treatment. The combination of MCT and WA could be a future area of interest in the personalization of treatment for people with psychosis. Additionally, Firth et al. (2018) found that once physical exercise is not offered by the mental health services, the adherence to the activity diminished by half. So, in the future, tailored interventions should also consider the inclusion of these activities in their service portfolio.

One limitation of the study is the absence of reevaluation of the measures long term. Due to limited resources, the study only offers measures post-intervention, that mark the effectiveness of the combined training. Nevertheless, we expect that the benefits would persist in the long-term considering previous MCT studies (Moritz et al., 2014). In the same way, patients in this study are selected from different mental health services, in different stages of the disorder, with different severity impact. This could impact the clinical response, due to heterogeneity. Nevertheless, this heterogeneity could contribute positively, allowing the implementation of the interventions in several settings and stages. Another limitation could be that we have not considered tobacco dependence as an exclusion criteria, due to its possible effect on cognition and symptoms. We have not excluded tobacco dependence because of the high prevalence of patients with schizophrenia that consume it. Including this as an exclusion criteria would severely limit the possibility of recruitment, and it would reduce ecological validity. However, it would be interesting if further studies consider this variable, due to its possible effect in cognitive function (Núñez et al., 2015; Hickling et al., 2018; Ding and Hu, 2021).

Further studies should consider the profile of response to each of these two interventions, or its combination, in order to design a more personalized approach in their treatment, based on stages of the illness and the patients’ needs.

In summary, these results could be of great importance for the understanding, prevention and treatment of schizophrenia and other psychotic disorders.

